# Efficacy and safety of hepcidin-based screen-and-treat approaches using two different doses versus a standard universal approach of iron supplementation in young children in rural Gambia: a double-blind randomised controlled trial

**DOI:** 10.1186/s12887-016-0689-4

**Published:** 2016-09-01

**Keywords:** Hepcidin, Iron supplementation, Iron deficiency, Iron deficiency anaemia, Anaemia, Safety, Children, Gambia, Sub-Saharan Africa

## Abstract

**Background:**

Iron deficiency prevalence rates frequently exceed 50 % in young children in low-income countries. The World Health Organization (WHO) recommended universal supplementation of young children where anaemia rates are >40 %. However, large randomized trials have revealed that provision of iron to young children caused serious adverse effects because iron powerfully promotes microbial growth. Hepcidin – the master regulator of iron metabolism that integrates signals of infection and iron deficiency – offers the possibility of new solutions to diagnose and combat global iron deficiency. We aim to evaluate a hepcidin-screening-based iron supplementation intervention using hepcidin cut-offs designed to indicate that an individual requires iron, is safe to receive it and will absorb it.

**Methods:**

The study is a proof-of-concept, three-arm, double blind, randomised controlled, prospective, parallel-group non-inferiority trial. Children will be randomised to receive, for a duration of 12 weeks, one of three multiple micronutrient powders (MNP) containing: A) 12 mg iron daily; B) 12 mg or 0 mg iron daily based on a weekly hepcidin screening indicating if iron can be given for the next seven days or not; C) 6 mg or 0 mg iron daily based on a weekly hepcidin screening indicating if iron can be given for the next seven days or not. The inclusion criteria are age 6-23 months, haemoglobin (Hb) concentration between 7 and 11 g/dL, z-scores for Height-for-Age, Weight-for-Age and Weight-for-Height > -3 SD and free of malaria. Hb concentration at 12 weeks will be used to test whether the screen-and-treat approaches are non-inferior to universal supplementation. Safety will be assessed using caregiver reports of infections, in vitro bacterial and *P. falciparum* growth assays and by determining the changes in the gut microbiota during the study period.

**Discussion:**

A screen-and-treat approach using hepcidin has the potential to make iron administration safer in areas with widespread infections. If this proof-of-concept study shows promising results the development of a point-of-care diagnostic test will be the next step.

**Trial registration:**

ISRCTN07210906, 07/16/2014

## Background

### Iron deficiency: global prevalence, health consequences, and barriers to progress in elimination

Iron deficiency (ID), leading to iron deficiency anaemia (IDA) and impaired neurocognitive development, remains the most pervasive nutritional deficiency worldwide [1]. Using currently accepted criteria the prevalence rates for IDA in young children frequently exceed 50 % in low-income countries (as is the case in The Gambia) resulting in impaired immunocompetence and brain development and thus leading to substantial loss of human potential [2]. Low cost iron supplements are efficacious in combatting IDA; thus in countries with anaemia rates of >40 %, WHO recommended universal supplementation of pregnant women and young children. However, in 2006, the Pemba Trial was prematurely terminated due to significant increases in the number of serious adverse outcomes and deaths in young children receiving iron-folic acid supplements [3]. This result was attributed to a malign interaction between iron, folic acid and malaria (since a parallel trial in a non-malarious area of Nepal revealed no increase in adverse outcomes), and WHO revised its policy guidance for iron supplementation to a more cautionary approach in areas with endemic malaria [4]. The new guidelines recommended adoption of targeted supplementation (a screen-and-treat approach) or the use of centralized or point-of-use food fortification using micronutrient powders, which was considered likely to be a safer option. However, recent studies, including a very large trial from a non-malarious area in Pakistan [5], have revealed important evidence of medically significant adverse outcomes associated with iron administration. It is assumed that all of these adverse outcomes may be attributable to host-pathogen competition for iron whereby supplemental iron has favoured pathogens more rapidly than their host. Thus there is an urgent need: a) to understand the pathways by which provision of iron favours pathogen virulence; and b) to use this knowledge to design safer modes for preventative and therapeutic provision of iron to infants and young children living in infectious environments in order to reduce infections and to allow maximal brain development.

### Evidence of detrimental effects of iron

Iron is unique among nutrients in being both essential and highly toxic. This tension has driven the evolution of complex systems for regulating iron absorption, and safely chaperoning it during transportation, storage and utilization in a vast majority of living organisms including humans of complex systems for regulating iron absorption, and safely chaperoning it during transport, storage and utilization [6]. The discovery of the iron-regulatory hormone hepcidin has thrown a sharp new focus on the adaptive/protective value of maintaining strict physiological control over iron absorption.

Initially the Pemba results were viewed with some scepticism in many quarters and/or were assumed to only affect malarious regions, as well as to be confined to supplementation as opposed to fortification. Yet, additional intervention trials have shown that administration of iron, either alone or as part of multiple micronutrient formulations, can lead to serious adverse effects as follows: a) a second trial in Tanzania showed an association between micronutrient supplements containing iron and the risk of malaria [7]; b) two trials of iron-fortified foods given to children in Côte d’Ivoire [8] and Kenya [9] caused significant adverse re-profiling of the gut microflora and evidence of intestinal inflammation; c) a large cluster-randomized single blind trial of iron-containing Sprinkles in 17,000+ Pakistani children has revealed significant increases in diarrhoea and pneumonia rates and a very significant increase in severe and bloody diarrhoea [5]. Finally, a recently published trial in young Ghanaian children receiving multiple micronutrient powders showed a trend towards lower malaria rates in the group receiving iron but an increase in hospitalisations among the iron-receiving group [10].

### The role of hepcidin – the master regulator of iron metabolism

Iron homeostasis, and its distribution within the body, is maintained by regulating absorption of iron through duodenal enterocytes and by controlling the rate of iron recycling through macrophages. Hepcidin is a small peptide hormone that binds to and causes the degradation of ferroportin, an iron export protein highly expressed by enterocytes and macrophages [11]. High levels of hepcidin thereby inhibit absorption of dietary iron and lock iron in macrophages, rapidly depleting serum iron (causing the protective hypoferraemia of the acute phase response) and lowering iron availability for erythropoiesis [12]. An abundance of genetic evidence in humans and experimental animals indicates that the ferroportin-hepcidin interaction is the dominant and non-redundant regulator of iron balance and iron distribution. Regulation of hepcidin is complex – iron accumulation induces hepcidin, providing a negative feedback loop to maintain homeostasis, but hepcidin levels are also increased by inflammatory signals arising during infections. Iron deficiency and erythropoietic drive suppress hepcidin, releasing iron from cellular stores and increasing dietary iron absorption. Importantly, each of these signals is variable, and the balance between them determines hepcidin synthesis. Thus, an iron deficient individual may have high serum hepcidin due to an acute infection, but on the other hand severe anaemia may suppress hepcidin even in the presence of inflammation.

### Iron redistribution as a component of innate defence against infection

It is widely accepted that the hypoferraemia of the acute phase response represents a highly conserved component of innate defence against a broad-spectrum of extracellular organisms that could elicit a rapidly fatal septicaemia if allowed unrestricted access to circulating iron. Several studies have proposed that iron-requiring intracellular organisms might have evolved their niche specificity precisely to capitalize upon the consequent iron-rich environment in macrophages [13]. Such interactions may play a significant role in explaining susceptibility to secondary infections. Experimental validation in animal and human studies may have important therapeutic implications.

### Hepcidin-guided iron supplementation

Because hepcidin reports on the balance of iron status and inflammation, and because hepcidin also determines how well oral iron is absorbed [11], low hepcidin levels indicate both a requirement for iron and an ability to utilize it if provided. Individuals with high hepcidin may be iron replete, or inflamed, or both, but will not be able to absorb oral iron efficiently. In our recently published paper this is clearly illustrated in young children, and our results suggest a cut-off of 5.5 ng/mL [14]. As discussed above, iron supplementation may provide limited benefit and be associated with deleterious consequences when given in the presence of inflammation. Therefore, providing an extra decision point (do not give iron unless hepcidin is below a cut-off level) in iron supplementation programs should make them both safer and more efficient. This will permit safe iron supplementation of young children in infectious areas allowing them to reach their full human potential.

### Multiple micronutrient powders (MNP)

In this trial we will use a micronutrient powder (MixMe) as it is used by the United Nations Children’s Fund and the World Food Programme. In a Cochrane systematic review (comprising eight large trials from a variety of settings, including malaria-endemic areas) assessing the effects and safety of home fortification with multiple micronutrient powders of foods consumed by children under two years, anaemia was reduced by 31 % and iron deficiency by 51 % [15]. The review found no difference in the effect of the intervention among children living in malaria endemic areas or areas with sporadic malarial cases. Based on this review WHO guidelines on home fortification were developed, strongly recommending home fortification with micronutrient powders to improve iron status and reduce anaemia among infants and young children 6-23 months of age [16].

More recently two other trials investigating the effect of MNP, one in Ghana and one in Pakistan, have been published. The trial in Pakistan showed significant increases in diarrhoea and bloody diarrhoea and pneumonia rates [5], whereas the trial in Ghana showed a trend towards lower malaria rates in the group receiving iron but an increase in hospitalisations among the iron group [10]. Although our trial will not be powered to assess morbidity we will monitor our children very closely by collecting morbidity data twice weekly.

### Study objectives

The *primary objective* is to evaluate whether weekly hepcidin-based screen-and-treat at 12 mg iron/day, screen-and-treat at 6 mg iron/day and 12 mg iron/day universal supplementation for 12 weeks are all non-inferior. The primary endpoint is Hb (measured using a Medonic haematology analyser in the laboratory) at day 84. Secondary endpoints related to the primary objectives are:i)Proportion of anaemia (Hb < 11 g/dL) at Day 84;ii)Proportion of iron deficiency (sTfR/logFerritin ratio > 3.2 or > 2.0 in the presence of inflammation (CRP > 5 mg/L) and ferritin < 12 μg/L or < 30 μg/L in the presence of inflammation) at Day 84;iii)Proportion of iron deficiency anaemia (Hb < 11 g/dL and sTfR/logFerritin ratio > 3.2 or > 2.0 in the presence of inflammation and ferritin < 12 μg/L or < 30 μg/L in the presence of inflammation) at Day 84;iv)Ferritin (only participants without inflammation), soluble transferrin receptor (sTfR), transferrin and transferrin saturation (TSAT) at Day 84.

The *secondary objectives* are the evaluation of i) the feasibility of adopting a hepcidin-based screen-and-treat approach to iron supplementation in young children (number of weeks supplemented with iron); ii) beneficial effects with screen-and-treat with respect to maternal reporting of child illness and safety indices (inflammatory and immune activation markers, faecal gut inflammation markers, gut microbiota, *ex-vivo* bacterial and *P. falciparum* growth); and iii) overall iron absorption over the 12 week supplementation period in the three study arms (sub-study).

## Methods/design

This paper describes the methodology of a randomized controlled non-inferiority trial comparing three different arms. Two arms are screen-and-treat approaches using hepcidin to indicate whether the body is ready to absorb iron and thus making it safe to give iron and the third arm is universal iron supplementation (recommended by WHO in non-malarial areas). Children randomized to the universal arm will get 12 mg iron daily for 12 weeks and children randomized to the screen-and-treat groups will receive 12 mg or 6 mg iron daily if their weekly hepcidin indicates a low value (<5.5 ng/mL), or 0 mg iron if their hepcidin indicates a high value (≥5.5 ng/mL) for the next seven days for a total of 12 weeks.

### Study site

Study participants will be recruited from 12 communities in Jarra West (Soma, Karantaba, Kani Kunda, Sankwia, Mansakonko, Pakalinding, Jenoi and Si Kunda) and Kiang East (Toniataba, Jiffin, Kaiaf and Genieri), in the Lower River Region of The Gambia. The communities around the town of Soma are approximately 170 km east of the capital Banjul. The town and some of the surrounding villages have an unreliable electrical power supply. All communities have access to borehole tap water at central places. Collected specimen samples will be transported in cold boxes to the MRC Keneba laboratory in West Kiang, The Gambia, for laboratory procedures.

### Participants

In total 393 healthy young children, aged 6-23 months, will be identified during child welfare clinics at the health facilities of Jarra West and Kiang East. After informed consent is obtained, children will have to meet the inclusion/exclusion criteria to be enrolled into the study. For inclusion children must be apparently healthy, 6-23 months old, not severely malnourished (z-scores for Height-for-Age, Weight-for-Age, Weight-for-Height > -3 SD), 7 g/dL ≤ Hb < 11 g/dL, free of malaria, resident in the study area, able and willing to comply with the study protocol, have no congenital disorders or chronic disease, not taking regular medication and not participating in another study.

In addition to the main study, ninety children will also be included into a sub-study (measuring iron absorption). The differences in the sub-study inclusion criteria are that eligible children must be aged between 6-8 months and 7 g/dL ≤ Hb < 12 g/dL when the stable isotope is administered at enrolment.

### Study design

This is a proof-of-concept, three-arm, double-blind randomized controlled non-inferiority trial. The three arms are:A)Supplementation with a MNP containing 12 mg iron dailyB)Supplementation with a MNP containing 12 mg iron/day if hepcidin is below 5.5 ng/mL, or MNP containing 0 mg iron/day if hepcidin is ≥ 5.5 ng/mL, based on a weekly hepcidin screening indicating whether iron can be given for the next 7 daysC)Supplementation with a MNP containing 6 mg iron/day if hepcidin is below 5.5 ng/mL, or MNP containing 0 mg iron/day if hepcidin is ≥ 5.5 ng/mL, based on a weekly hepcidin screening indicating whether iron can be given for the next 7 days

### Recruitment, enrolment and randomisation

A summary chart of all study procedures is illustrated in Fig. 1. Mothers/Guardians of the young children identified during child welfare clinics at the selected health centres will be visited at home where the study will be clearly explained. Demographic information will be collected once the child’s mother/guardian has signed the informed consent form. If the inclusion criteria are met, the child will be invited for further eligibility screening during which they will be physically examined. Height, weight, head circumference, mid-upper arm circumference and triceps skinfold thickness will be measured and a finger prick blood sample for Hb and rapid diagnostic test (RDT) for malaria will be taken. If Hb is ≥ 7 and < 11 g/dL, and the RDT is negative, a venous blood sample of 5 mL will be collected. The mother will then be asked to collect a stool sample from the child within the next two days. Enrolled children will be randomized to one of the three study arms (equal number in each arm) using a block randomization, balanced by Hb concentration and age, to minimise potential baseline imbalance.

**Fig. 1 Fig1:**
[figure not shown]
Main study flow chart. Legend: Hb, Haemoglobin; Fe, Iron; MNP, Micronutrient powder

Children with Hb < 7 g/dL will not be enrolled and will be referred to the regional health centre for treatment according to national guidelines. Children with Hb ≥ 11 will not be enrolled as they do not need iron supplementation. Malaria positive children (positive RDT and confirmation by blood film) will not be enrolled and will be treated according to national guidelines.

The 90 children additionally participating in the sub-study will be recruited as described above, but the enrolment day procedure is slightly different (Fig. 2). Children eligible for the sub-study will not have a venous blood sample drawn, but will receive the stable isotope dose on the day of enrolment. They will then be followed up monthly using a morbidity questionnaire until their participation in the main study (earliest seven months after stable isotope administration). This period is to ensure that the stable isotope has homogenously equilibrated with total body iron. On the day of enrolment into the main study, these children will undergo the same procedure as described above for the main study.

**Fig. 2 Fig2:**
[figure not shown]
Sub-study flow chart and timing. Legend: mo, month

Recruitment into the sub-study has started in April 2014 while the first cohort for the main study was recruited in May 2014.

### Follow-up

Field workers will visit all children daily during the 12 weeks supplementation period in order to supervise the MNP administration and to check on the children’s health status. Twice weekly morbidity data (including questions regarding fever, diarrhoea, vomiting, cough, any other illness, appetite and any medication taken and assessment of body temperature) will be captured. If a child is found unwell, the study nurse will check on the child and decide on the appropriate treatment. Each week every child will be screened using a finger prick blood sample (200 μL) to determine their hepcidin and Hb level and their malaria status. Hb and RDT testing will be directly conducted in the field whereas hepcidin analysis will be performed in the laboratory in Keneba. On the following day hepcidin results are used to allocate the MNP for the next seven days for each child. Supervised MNP administration will be conducted by the field workers daily at participant’s homes. During the trial, children found with a positive RDT will be further tested with a blood film and treated according to national guidelines if malaria is confirmed. Any child with a Hb < 7 mg/dL will be excluded and referred to the next health centre for management according to national guidelines.

On Days 14 and 84 another faecal sample and on Days 49 and 84 another venous blood sample (5 mL) will be collected, instead of a finger prick blood sample. All blood samples will be kept in a cool chest after collection and transported to Keneba on ice. An additional blood sample will be collected on Day 168 from the children also participating in the sub-study. Height, weight, head circumference, mid-upper arm circumference and triceps skinfold thickness will be re-measured at Days 49 and 84, as well as Day 168 (for the sub-study children).

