### Sample size

This is a non-inferiority trial to evaluate efficacy and the primary endpoint is Hb concentration (measured using a Medonic haematology analyser in the laboratory) at day 84. Based on a SD of 1.15 g/dL of the mean Hb value of children at 24 week of age, from a previous trial conducted at Keneba [19], a sample size of 131 participants in each of the three arms is required using a 1-sided α of 2.5 and a Bonferroni correction to adjust for multiple testing. A total sample size of 393 children followed up for 12 weeks, with a drop-out of less than 15 %, will provide 80 % power to establish that:arm B is non-inferior to arm A on the primary endpoint (Hb concentration at Day 84) defined as the upper 98.3 % confidence limit for the difference in mean Hb being not greater than 0.5 g/dL (non-inferiority margin), the smallest value considered to be of public health relevancearm C is non-inferior to arm A at the same level as abovearm C is non-inferior to arm B at the same level as above

For the sub-study, the power calculation for iron absorption is based on the data from Fomon et al. [20] in infants. Twenty subjects per group are required to resolve a difference in absorbed iron of 0.080 mg/d between the control and intervention period, based on a SD of 0.13 mg/d (paired t-test). The between group difference that we estimate being able to resolve is 0.12 mg/d absorbed iron (unpaired *t*-test). Lower variability is expected in the calculated k_abs_ values, which are independent from Hb, body weight, and iron status, the main contributors to variability in the calculation of iron absorption. Considering attrition due to the long time span of at least 7 months between recruitment (administration of stable isotope dose) and participation in the main study, 30 subjects per group will be recruited.

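### The on-study haemoglobin limit for exclusion and referral is printed in mg/dL instead of g/dL, a factor of 1000 too low

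*Protocol article*

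**What the plan says.** In Follow-up, after describing the weekly finger-prick screening, the protocol article gives the rule for severe anaemia arising on study: "Any child with a Hb < 7 mg/dL will be excluded and referred to the next health centre for management".

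The same limit of 7 appears in four other places, each time in g/dL:

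- Abstract, Methods: "haemoglobin (Hb) concentration between 7 and 11 g/dL".
- Participants: "7 g/dL ≤ Hb < 11 g/dL, free of malaria".
- Recruitment, enrolment and randomisation, screening step: "If Hb is ≥ 7 and < 11 g/dL, and the RDT is negative".
- The text following Fig. 1, which is the counterpart at enrolment of the Follow-up rule: "Children with Hb < 7 g/dL will not be enrolled and will be referred to the regional health centre".

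The planning assumption in Sample size is on the g/dL scale too: "Based on a SD of 1.15 g/dL of the mean Hb value of children". The article gives no reason for using another unit in Follow-up.

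**The concern.** The Follow-up sentence is an operative rule. It decides when a child leaves the trial and is sent for treatment. Read literally, it sets a limit that cannot be reached, so no child would ever be excluded or referred under it.

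The situation it covers is foreseeable. Children are already anaemic at entry and may be enrolled at exactly 7 g/dL. In the two screen-and-treat arms a child receives no iron in any week when hepcidin is 5.5 ng/mL or higher. A weekly reading below 7 g/dL is therefore quite possible, and the rule should say correctly what then happens.

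In the text shown, this is the only numeric on-study haemoglobin limit for safety. A reader who wants the right value has to infer it from the enrolment rule.

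**Working it through.** **Inputs**

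- On-study limit as printed: 7 mg/dL (Follow-up).
- Lower limit at entry: 7 g/dL (Abstract; Participants; Recruitment, enrolment and randomisation; text following Fig. 1).
- Planning values: SD 1.15 g/dL, margin 0.5 g/dL, one-sided alpha 2.5 % with Bonferroni correction for three comparisons, power 80 %, drop-out below 15 % (Sample size; Statistical analysis).

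**Unit conversion**

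1 g = 1000 mg, so 7 mg/dL ÷ 1000 = 0.007 g/dL.

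Ratio of the entry limit to the printed limit: 7 ÷ 0.007 = 1000.

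The entry limit expressed in the printed unit: 7 g/dL × 1000 = 7000 mg/dL.

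**The two referral rules side by side**

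| | At enrolment (text following Fig. 1) | On study (Follow-up) |
|---|---|---|
| Number | 7 | 7 |
| Unit | g/dL | mg/dL |
| Action | not enrolled, referred | excluded, referred |
| Standard of care | national guidelines | national guidelines |

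The rules share the number, the direction, the referral and the standard of care. Only the unit differs. With g/dL in Follow-up, the on-study limit coincides with the entry limit.

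**Does the slip reach the sample size?**

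The usual formula for non-inferiority of two means, per arm, is n = 2 × SD² × (z₁₋α + z₁₋β)² ÷ margin².

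- One-sided alpha after correction: 0.025 ÷ 3 = 0.00833, so z = 2.394.
- Power 80 %: z = 0.842.
- n = 2 × 1.15² × (2.394 + 0.842)² ÷ 0.5² ≈ 110.8, rounded up to 111.
- Allowing for 15 % drop-out: 111 ÷ 0.85 = 130.6, rounded up to 131 per arm.
- Total: 3 × 131 = 393.

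This reproduces the article's figures of 131 and 393. The exclusion limit does not enter the formula, so correcting it changes nothing here.

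**The case against.** The strongest reply is that this is a proofreading slip with only one sensible reading. The printed value is physically impossible, the matching enrolment rule stands nearby with the right unit, and nobody could apply the misprint in earnest.

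The article is also unlikely to be what field staff worked from. It was published in September 2016, whereas recruitment began in April and May 2014, and it condenses a full protocol that is not shown. Nothing in the text suggests that the field procedures carry the wrong unit. Fig. 1 is not shown either and might restate the rule.

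Finally, child safety does not hang on this sentence. Field workers visit daily, morbidity is recorded twice weekly, haemoglobin and malaria are tested weekly, and for illness the article adds: "If a child is found unwell, the study nurse will check on the child and decide on the appropriate treatment".

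Most of this stands, and it is why the point is minor. It also limits the claim to the text shown. It does not make the printed figure right: an impossible limit in an operative rule is an error in the Methods, and neither an unseen document nor an unseen figure corrects the sentence.

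**Conclusion.** The point holds, as a minor one. The on-study exclusion and referral limit is wrong by a factor of 1000 as printed (0.007 g/dL against an evident intention of 7 g/dL), and it contradicts the limit of 7 g/dL stated in four other places.

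That 7 g/dL was meant is an inference, but a very safe one, since it rests on the matching enrolment rule and on the consistent use of g/dL for haemoglobin elsewhere. The article gives no evidence that the wrong unit was used in the field or that any child was affected. Sample size, alpha, non-inferiority margin and planned analyses are unaffected.

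**What to change.** In Follow-up, replace mg/dL with g/dL, so that the rule applies to any child with haemoglobin below 7 g/dL. As a precaution, confirm that the full protocol and the field procedures state this limit in g/dL.

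The cost is a one-word correction and a short document check. No change to design or analysis follows.

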### Statistical analysis

The primary haemoglobin outcome (measured using a Medonic haematology analyser in the laboratory) at day 84 will be tested for non-inferiority by performing a per-protocol analysis with a 5 % significance level, adjusted using the Bonferroni correction to account for three main comparisons. We will also repeat the main analysis using the intention-to-treat population as a confirmatory analysis.

Secondary outcome analysis of continuous variables (ferritin, sTfR, transferrin, TSAT, CRP, AGP, calprotectin, *ex-vivo* growth, gut microbiota, number of weeks supplemented) will be done using mixed-effect models with individuals treated as a random effect, and secondary outcome analysis of categorical variables (anaemia, ID and IDA) will be modelled using mixed-effect logistic regression. Interactions between study arm and time in the study will be investigated.

Morbidity data will be analysed using mixed-effect models controlled for possible confounders.

Exploratory analysis will be performed using serum iron.

All data will be analysed using Stata v12.1 (StataCorp, LP, USE, http://www.stata.com) and statistical significance will be defined as *p* < 0.05, unless stated otherwise.

In the sub-study, the linear regression of log^57^A^t^ (^57^A^t^ = abundance at time t) against time will be calculated for each subject belonging to the three different groups for the period of Day 0 to Day 84 (with a midpoint sample at day 49). The slope (k_abs_) of the regression reflects the absorption of iron per unit of time. The difference in the slopes between the groups will be equivalent to the average iron absorption over time in each group (k_abs_ in groups A, B, and C, respectively).

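### Excluding children whose Hb falls below 7 g/dL selects the primary per-protocol set on the primary variable, a modest bias towards non-inferiority if a screen-and-treat arm is truly worse

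*Protocol article*

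**What the plan says.** All in the Protocol article:

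- **Participants.** Entry requires "7 g/dL ≤ Hb < 11 g/dL, free of malaria", so some children may start at or just above the later exclusion threshold.
- **Follow-up.** Hb is checked weekly in all arms: "Each week every child will be screened using a finger prick blood sample (200 μL) to determine their hepcidin and Hb level". The rule that acts on it is: "Any child with a Hb < 7 mg/dL will be excluded and referred to the next health centre for management according to national guidelines". The unit must be g/dL, as in the enrolment criteria.
- **Statistical analysis.** The primary outcome "at day 84 will be tested for non-inferiority by performing a per-protocol analysis with a 5 % significance level", Bonferroni-adjusted for three comparisons. Then: "We will also repeat the main analysis using the intention-to-treat population as a confirmatory analysis".
- **Sample size.** The criterion is "the upper 98.3 % confidence limit for the difference in mean Hb being not greater than 0.5 g/dL (non-inferiority margin").

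**The concern.** The safety rule and the choice of primary analysis set work against each other. A child whose weekly Hb drops below 7 g/dL is excluded, has not completed 12 weeks on its arm, and would ordinarily be left out of a per-protocol set. The primary set is then selected after randomisation, on the primary variable, and only at its low end.

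If the arms are truly equal, the exclusions balance. If a screen-and-treat arm is truly worse, more of its children cross 7 g/dL, and its remaining mean is raised more than that of the universal arm. The deficit shrinks, which in a non-inferiority trial favours success. The children removed are those with the worst result on the trial's own efficacy variable. The secondary endpoint "Proportion of anaemia (Hb < 11 g/dL) at Day 84" would lack their values too if they are not followed.

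The intention-to-treat repeat repairs this only if these children have a Day 84 Hb. Even then, that value partly reflects the treatment given after referral.

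**Working it through.** **Inputs from the protocol.** SD 1.15 g/dL, margin 0.5 g/dL, one-sided 2.5 % with Bonferroni over three comparisons, 80 % power, drop-out below 15 %, 131 per arm (Sample size); entry Hb 7 to below 11 g/dL (Participants); weekly check and threshold 7 (Follow-up).

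**Assumed, because the protocol gives no figure.** Mean Hb, gain on universal iron, week-to-week variation, and a loss spread evenly over children.

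**1. Reproduce the plan's sample size.** The level is 0.025/3 = 0.00833, so z = 2.394; for 80 % power z = 0.842.

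n = 2 × 1.15² × (2.394 + 0.842)² / 0.5² = 110.8, so 111 per arm. 111/0.85 = 130.6, so 131 per arm and 393 in total. This matches, so 0.83 % is the per-comparison error behind the design.

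**2. Error without exclusions.** P(declare non-inferior) = Φ((0.5 − d)/SE − 2.394), where d is the expected difference (universal minus comparator) in the analysed set. At a true loss of 0.5 with all children kept, d = 0.5 and P = Φ(−2.394) = 0.83 %.

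**3. Simple check: Day 84 Hb normal with SD 1.15, cut at 7.** The mean of the retained children is m + 1.15 × φ(a)/(1 − Φ(a)), with a = (7 − m)/1.15.

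Example with universal-arm mean 9.5 and comparator 9.0:
- Universal: a = −2.174, 1.5 % removed, retained mean 9.544.
- Comparator: a = −1.739, 4.1 % removed, retained mean 9.105.
- d = 0.438. With 111 per arm, SE = 1.15 × √(2/111) = 0.154, so P = Φ(0.062/0.154 − 2.394) = 2.3 %.

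| Universal-arm mean (g/dL) | Removed, universal vs worse arm | d (g/dL) | False non-inferiority, 111 per arm |
|---|---|---|---|
| 9.5 | 1.5 % vs 4.1 % | 0.438 | 2.3 % |
| 10.0 | 0.4 % vs 1.5 % | 0.471 | 1.4 % |
| 10.5 | 0.1 % vs 0.4 % | 0.489 | 1.0 % |
| 11.0 | 0.03 % vs 0.1 % | 0.497 | 0.9 % |

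With 131 per arm the errors are 2.6, 1.4, 1.0 and 0.9 %.

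**4. Weekly simulation: exclusion at the first weekly Hb below 7, true Day 84 loss 0.5, spread evenly.**
- *131 per arm.* Entry mean 9.5 or 10.0, total SD 1.15, restricted to 7 to below 11; gain on universal iron 0 or 0.5 g/dL; week-to-week SD 0.4 or 0.6. Excluded: 1 to 8 children against 2 to 14. d = 0.44 to 0.49, error 1.1 to 2.9 %. With 111 per arm the error is 1.2 to 2.8 %. Without exclusion the same settings give 0.8 to 0.9 %.
- *111 per arm, other variance settings (Day 84 SD 1.04 to 1.22), same entry means and gains.* Excluded: 0.4 to 7.3 % against 1.0 to 12.5 %. d = 0.415 to 0.484, error 1.1 to 3.2 %. The extreme needs entry mean 9.5, no gain on universal iron and the larger variance setting.
- *Gain of 1.0 g/dL on universal iron.* Error 1.0 to 1.3 %.

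**5. Direction.** With a true deficit, no even-loss setting tried moved the difference away from zero. With no true difference, exclusions balance and there is no bias.

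**The case against.** **The analysis sets are not defined here.** The exclusion sentence is a clinical rule and does not say that the child leaves an analysis set. Definitions of the per-protocol and intention-to-treat sets, and counts of withdrawals, are commonly left to the full protocol or SAP. This stands in part: that the child drops out of the primary set is the ordinary reading, not a stated fact, and the absence of definitions is not a fault of the article. What remains is the combination of two stated rules. If excluded children are not followed to Day 84, no later definition can recover their values.

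**An intention-to-treat repeat is planned.** It is a partial safeguard, but it is called confirmatory, with no stated consequence if the two analyses disagree, and it depends on Day 84 values being collected.

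**The trigger is a field HemoCue reading, the endpoint a Medonic value.** The link is therefore by correlation. The weekly simulations include week-to-week noise and the bias persists, though smaller than if each excluded child were counted at just under 7 g/dL on Day 84. A child caught on one low reading tends to drift back up.

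**A reader might infer a much larger error.** Concentrating the loss in a quarter of the children, at 2.0 g/dL each, pushes the error to between 5 % and 29 %. The documents do not support that setting. Under Hepcidin-guided iron supplementation, children with high hepcidin are said to absorb oral iron poorly, so withholding it should cost them little. Under The role of hepcidin, iron deficiency and severe anaemia are said to lower hepcidin, so a child drifting towards 7 g/dL would tend to screen low and be given iron again. The upper end also implies about 21 of 131 (16 %) excluded in the worse arm for low Hb alone, above the 15 % ceiling on all drop-out. Likewise, picking exclusion counts such as 2 against 8 only illustrates the arithmetic, since no such counts are in the protocol.

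**Conclusion.** The point holds as a modest bias with a clear direction. Read in the ordinary way, the Follow-up and Statistical analysis sections together select the primary set on the primary variable, and this favours non-inferiority when a screen-and-treat arm is truly worse.

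At a true loss of 0.5 g/dL spread evenly, the expected difference becomes about 0.44 to 0.50 g/dL (0.42 in the most variable setting tried). The per-comparison error rises from 0.83 % to about 0.9 to 3 %. The upper end needs a low mean Hb and no gain on universal iron. The effect is negligible with universal-arm Hb near 11 g/dL and nil when the arms are equal.

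These figures rest on assumed means, gains and week-to-week variation. It would be wrong to conclude that the primary test is grossly anti-conservative, that referral at Hb below 7 g/dL is improper, or that the trial is bound to lose these children from every analysis. The change is worth making because it is cheap and because Day 84 values not collected cannot be recovered.

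**What to change.** **Follow-up section.** Correct the unit and replace exclusion with: a child with Hb below 7 g/dL stops the study powder, is referred under national guidelines, and stays in follow-up with Day 84 Hb measured.

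**Statistical analysis section.** State that:
- stopping for Hb below 7 g/dL is an outcome, not a reason for removal from the analysis;
- these children stay in the intention-to-treat analysis with their measured Day 84 Hb;
- non-inferiority is declared only if the intention-to-treat and per-protocol analyses agree;
- a sensitivity analysis of both sets uses the Hb that triggered referral as the Day 84 value;
- the number of children with Hb below 7 g/dL is reported by arm.

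**Cost.** No extra children and a few more Day 84 samples. Measured Day 84 Hb will partly reflect referral treatment, which also dilutes a deficit; the sensitivity analysis covers that. It mixes HemoCue and Medonic values and ignores recovery. Made primary, it would cost about 1 to 9 points of power when the arms are equal, so it belongs as a sensitivity analysis. Requiring both analyses to agree can only lower power; that loss was not computed.
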